## Abstract

**Background:**

Patients with chronic kidney disease (CKD) reportedly show dysbiosis, which is the imbalance of gut microbiome. Dysbiosis increases the uremic toxin level in the intestine, and uremic toxins transfer into the blood, causing CKD progression. Sake lees, a traditional Japanese fermented food, may help reduce uremic toxins by altering the gut microbiome. Additionally, D-alanine, which is present in sake lees, may have a renoprotective effect. The present pilot study aims to evaluate the effect of adding sake lees to the standard CKD dietary therapy in reducing blood uremic toxins.

**Methods:**

This pilot study is a single-center, open-label, randomized controlled trial. Twenty-four patients with CKD will be enrolled and allocated 1:1 to the intervention and control groups. The intervention group will receive standard CKD dietary therapy with an additional intake of 50 g of sake lees per day for 8 weeks, whereas the control group will only receive standard CKD dietary therapy. The primary endpoint is the change in serum indoxyl sulfate after 8 weeks. The secondary endpoint is the plasma D-alanine and fecal microbiome changes.

**Conclusion:**

This pilot study provides insight into the development of a new diet focused on gut microbiome and D-amino acids in patients with CKD.

**Clinical trial registration:**

This protocol was approved by the Clinical Trial Review Board of Kanazawa University Hospital on October 27, 2022 (2022-001 [6139]) and available to the public on the website of the Japan Registry of Clinical Trials on November 22, 2022 (jRCT1040220095).

**Supplementary Information:**

The online version contains supplementary material available at 10.1007/s10157-023-02450-x.

## Introduction

Patients with chronic kidney disease (CKD) reportedly show dysbiosis, which is the imbalance of gut microbiome [1]. Dysbiosis increases the uremic toxin levels in the intestine, and uremic toxins transfer into the blood, causing CKD progression [2]. Recently, CKD treatment focusing on the gut microbiome has been performed in clinical trial [3]. Probiotics and prebiotics are considered the primary treatment candidates for dysbiosis. For example, a type of probiotics or prebiotics can alter the gut microbiome in CKD patients and can reduce the blood uremic toxins or blood urea nitrogen levels [4, 5].

Sake lees is a fermented food commonly consumed in Japan [6]. It is generated in the fermentation process of Japanese sake (rice wine). Sake lees contains bacteria and dietary fiber and improves the gut microbiome of patients with chronic constipation [7]. Additionally, sake lees also contains D-alanine and D-serine, which are mainly produced by bacteria [8, 9] and could potentially have renoprotective effects [8, 9].

Based on these backgrounds, sake lees may have renoprotective effects by improving the gut microbiome and producing D-alanine and D-serine by the bacteria present in sake lees. To evaluate the renoprotective effects, it is necessary to monitor the blood uremic toxin levels, which may be altered by sake lees intake and accelerate CKD progression.

This pilot study aims to evaluate whether the addition of sake lees to the standard CKD dietary therapy decreases the blood uremic toxin levels as compared to the standard CKD dietary therapy only.

## Materials and methods

### Study setting

This pilot study is a single-center, open-label, randomized controlled trial with a target sample size of 24 participants. Figure 1 shows a summary of the trial. The main eligibility criterion is meeting the diagnostic criteria for CKD. After a 2-week run-in period, participants will be allocated 1:1 to the intervention and control groups. During the intervention period, the intervention group will receive standard CKD dietary therapy with an additional intake of 50 g of sake lees per day for 8 weeks, whereas the control group will only receive the standard CKD dietary therapy. After the intervention, both groups will be observed for a period of 4 weeks. The primary endpoint is the change in serum indoxyl sulfate. The secondary endpoints are the changes in the serum p-cresyl sulfate and plasma D-alanine levels as well as fecal microbiome. The measurements for the endpoints will be performed at baseline and at 8 and 12 weeks.

**Fig. 1 Fig1:**
[figure not shown]
The study flowchart. *CKD* chronic kidney disease, *ECOG* Eastern Cooperative Oncology Group, *FAS* full analysis set, *PPS* per protocol set

### Eligibility criteria

The inclusion criteria are as follows: age ≥20 years, estimated glomerular filtration rate (eGFR): 15 to <60 mL/min/1.73 m^2^, meeting the diagnostic criteria for CKD [10], performance status score (Eastern Cooperative Oncology Group [11]) of 0, and regular visits at the hospital. The exclusion criteria are as follows: on dialysis therapy, post-renal transplant, cancer-bearing, body mass index of <16 kg/m^2^, immunocompromised, inflammatory bowel disease, liver dysfunction, daily use of antibiotics, history of antimicrobial therapy within the past 4 weeks of study entry, daily intake of sake lees, alcohol intolerance, history of alcohol dependence, and physician’s determination of unfitness for this study.

### Intervention and control

The intervention group will receive the standard CKD dietary therapy with an additional intake of 50 g of sake lees per day for 8 weeks. The standard CKD dietary therapy consists of energy 30–35 kcal/kg-standard body weight/day, protein 0.6–1.0 g/kg-standard body weight/day, and salt <6 g/day, according to the guidelines for CKD dietary therapy [12]. The control group will not be adjusted for the addition of energy or protein to the intervention group. Potassium and phosphorus should be restricted as needed. The control group will only receive the standard CKD dietary therapy for 8 weeks and is prohibited from taking sake lees. Both groups are prohibited from consuming functional foods or drugs labeled to improve the intestinal environment during the protocol period. The consumption of yogurt or other common fermented foods is acceptable. During the protocol period, the additions or dosage changes of drugs originally taken are allowed. The use of antimicrobials or intestinal agents during the protocol period is a protocol violation.

### Intervention details

The sake lees that will be used in this study are made from a Japanese sake called “Kakuma no Sato” and are purchased from the manufacturer in Japan. According to the nutritional information on the product label, the main nutrients per 100 g of sake lees are as follows: energy: 209 kcal, protein: 7.2 g, fat: 0.6 g, carbohydrates: 30.8 g, salt: 0 g, dietary fiber: 5.2 g, and alcohol: 8 g. All participants will use the same lot of sake lees. We will prepare a sake lees recipe to make it easy for the participants to cook sake lees. The participants will also be allowed to cook sake lees as they liked. The sake lees amount per meal and the mealtime will be left to the participants. The participants will record their sake lees intake daily on a designated recording form. The recording form will also include the frequency of bowel movements, form of stool, and use of laxatives. Nutritional guidance by registered dietitian will be provided at included, baseline, and 8 and 12 weeks.

### Endpoints

The primary endpoint of this study is the level of blood indoxyl sulfate, a metabolite of intestinal origin, and a surrogate marker of renal function [13]. Given that this study hypothesized changes in the levels of intestinal uremic toxins due to sake lees intake, the primary endpoint is the change in serum indoxyl sulfate concentration at baseline and at 8 weeks. Table 1 shows the list of secondary endpoints. The secondary endpoints include the changes in serum p-cresyl sulfate and plasma D-alanine levels and fecal microbiome. Changes in eGFR and proteinuria will not be considered endpoints in this study, because the intervention period of 8 weeks is too short to expect significant changes in those parameters. The measurement schedule for each outcome variable is shown in Table 2. Basic data, such as serum creatinine and potassium levels, will also be assessed for eligibility verification or safety purposes.

**Table 1 Tab1:** Primary and secondary endpoints

	Sample	Endpoints
Primary	Blood	Serum indoxyl sulfate
Secondary	Blood	Serum p-cresyl sulfate
		Plasma D-alanine
		Plasma D-serine
	Feces	Indole
		P-cresol
		Acetic acid
		Propionic acid
		Butyric acid
		pH
		Microbiome (16S rRNA gene sequence analysis)
	Urine	Urinary protein
		pH
		Estimated salt excretion
		MCP-1
		KIM-1
	Questionnaire	CSS
		PAC-QOL
		FFQg

*MCP-1* monocyte chemotactic protein 1, *KIM-1* kidney injury molecule 1, *CSS* constipation scoring system, *PAC-QOL* patient assessment of constipation quality-of-life questionnaire, *FFQg* food frequency questionnaire based on food groups

**Table 2 Tab2:** Measurements schedule

	Screened for eligibility	Entry	Baseline	Week 8	Week 12
Check the criteria	✓				
Basic data	✓		✓	✓	✓
Medical questionnaire		✓			
Recording form			✓	✓	✓
*Outcomes*					
Blood					
Serum indoxyl sulfate			✓	✓	✓
Serum p-cresyl sulfate			✓	✓	✓
Plasma D-alanine			✓	✓	✓
Plasma D-serine			✓	✓	✓
Feces					
Indole			✓	✓	✓
P-cresol			✓	✓	✓
Acetic acid			✓	✓	✓
Propionic acid			✓	✓	✓
Butyric acid			✓	✓	✓
pH			✓	✓	✓
Microbiome			✓	✓	✓
Urine					
Urinary protein			✓	✓	✓
pH			✓	✓	✓
Estimated salt excretion			✓	✓	✓
MCP-1			✓	✓	✓
KIM-1			✓	✓	✓
Questionnaire					
CSS			✓	✓	✓
PAC-QOL			✓	✓	✓
FFQg		✓		✓	

*MCP-1* monocyte chemotactic protein 1, *KIM-1* kidney injury molecule 1, *CSS* constipation scoring system, *PAC-QOL* patient assessment of constipation quality-of-life questionnaire, *FFQg* food frequency questionnaire based on food groups

### Sample size

The sample sizes for the intervention and control groups will be 12 cases each. The number of cases is set based on feasibility and the recommended number of cases for the pilot study [14]. The maximum sample size allowed for entry will be 30 in total for both groups, considering the possibility of discontinuations.

### Recruitment, run-in, and randomization

Recruitment will be conducted at the Department of Nephrology and Rheumatology, Kanazawa University Hospital (Kanazawa City, Ishikawa, Japan). The patients who met the eligibility criteria will be given a 2-week run-in period to eliminate the influence of food or drugs on the intestinal environment. During the run-in period, the intake of sake lees is prohibited. The participants are prohibited from consuming functional foods or drugs labeled to improve the intestinal environment. The consumption of yogurt or other common fermented foods is acceptable. A dynamic allocation strategy using the minimization method will be used for randomization. The allocation ratio is set at 1:1, with allocation adjustments for age (<75 or ≥75 years) and eGFR (15 to <30 or 30 to <60 mL/min/1.73 m^2^). Subjects will be automatically randomized using a web-based case registration and randomization system.

### Data and sample collection

Data will be collected at baseline and at 8 and 12 weeks. In addition to the primary and secondary endpoints, basic data, such as age, sex, blood pressure, height, body weight, skeletal muscle mass, body fat mass, red blood cell count, hemoglobin, hematocrit, and aspartate aminotransferase, alanine aminotransferase, blood urea nitrogen, serum creatinine, serum uric acid, serum potassium, serum phosphorus, serum albumin, and total cholesterol levels, will be collected. Participants’ bowel movements will be assessed using a constipation scoring system [15] and a patient-rated constipation quality-of-life questionnaire [16]. At baseline and week 8, data on nutritional intake (energy, protein, salt, and dietary fiber) will be collected using a food frequency questionnaire based on food groups [17]. The participants will record the amount of their sake lees intake and compliance status of prohibited food or drugs during the protocol period. This record will be collected by the research group on week 12.

Specimens will be collected at baseline and 8 and 12 weeks. The plasma and serum will be centrifuged and stored at −80 °C. Participants will take a defined meal for dinner the day before the blood sampling and the morning of the blood sampling. Detailed information regarding the defined meal is provided in **Supplementary Fig. 1**. The feces for indole and p-cresol analysis are sampled by participants in a stool container using a specimen-collection spoon. The stool container will be collected and stored at −80 °C. The feces for gut microbiome analysis will be sampled using a brush kit (TechnoSuruga Laboratory Co., Ltd., Shizuoka, Japan) and stored refrigerated. Spot urine will be sampled at the time of the visit and centrifuged, and the supernatant will be stored at −80 °C.

### Statistical analysis

The primary and secondary endpoints will be tested using unpaired *t* tests for the measurement changes from baseline to week 8 between the intervention and control groups. As a secondary analysis, the changes between the intervention and control groups at baseline, 8 and 12 weeks will be tested using repeated measures analysis of variance. A multivariable regression analysis will be performed on the change in serum indoxyl sulfate levels from baseline to week 8, using age, sex, and eGFR at baseline as covariates. A two-tailed significance level of *p* < 0.05 will be used.

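### Allocation is minimized on age and eGFR, but the main tests are unadjusted t tests: conservative, with a modest loss of efficiency if those factors predict the 8-week change

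*Protocol article*

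**What the plan says.** All references are to the protocol article.

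- **Allocation** (Recruitment, run-in, and randomization): "A dynamic allocation strategy using the minimization method will be used for randomization". The ratio is 1:1, with "allocation adjustments for age (<75 or ≥75 years) and eGFR (15 to <30 or 30 to <60 mL/min/1.73 m^2".
- **Main test** (Statistical analysis): "The primary and secondary endpoints will be tested using unpaired *t* tests for the measurement changes from baseline to week 8", comparing the two groups, at a two-sided 5% level. No covariate is named.
- **Other analyses** (same section): the course over baseline, week 8 and week 12 "will be tested using repeated measures analysis of variance", again with no allocation factor named. For indoxyl sulfate only, a multivariable regression of the same change is added, "using age, sex, and eGFR at baseline as covariates". The text does not say whether treatment group is in that model.
- **Size** (Sample size): 12 per arm, chosen on feasibility and a pilot-study recommendation. No effect size, SD or power is given.

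**The concern.** Minimization makes the arms alike on age group and eGFR group, so the part of the outcome variation that those factors explain largely cancels from the difference in means. An unadjusted t test does not know this. Its pooled SD still contains that variation, so its standard error describes a less balanced trial than the one that was run. Whenever the factors predict the change, the confidence interval is too wide and the p-value too large.

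The plan itself treats these factors as relevant twice, once in allocation and again in the regression. The Endpoints section also describes indoxyl sulfate as "a metabolite of intestinal origin, and a surrogate marker of renal function", which makes eGFR a natural candidate. With 12 patients per arm, a few points of power may matter. For the secondary endpoints, the article names no adjusted analysis beside the t test.

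**Working it through.** **Inputs from the article:** 12 per arm, two-sided alpha 0.05, minimization on two binary factors, t test on change. There is no stated power figure to reproduce.

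**Assumptions (not in the article):** within-arm SD of change = 1; true effect 1.0 SD; the two factors together explain a share R² of the variance of change, split equally; each factor level has prevalence 0.4; minimization follows the preferred arm with probability 0.9; all 24 patients analyzed.

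**Step 1: what the t test reports.** SE = √(1/12 + 1/12) = 0.408 SD on 22 df. Exact power at 1.0 SD is 65%.

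**Step 2: the true spread of the estimate.** With near-perfect balance it is 0.408 × √(1 − R²).

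- R² = 0.1: 0.408 × 0.949 = 0.387. The reported SE is too wide by a factor 1/√0.9 = 1.05.
- R² = 0.2: 0.408 × 0.894 = 0.365. The factor is 1/√0.8 = 1.12.

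**Step 3: type I error, approximately.** The 5% critical value (2.074 on 22 df) acts as if multiplied by that factor.

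- R² = 0.1: P(|t| > 2.074 × 1.054 = 2.19) = 4.0%.
- R² = 0.2: P(|t| > 2.074 × 1.118 = 2.32) = 3.0%.

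**Step 4: power of a model with group and both factors (20 df).** Noncentrality = 1.0 / (0.408 × √(1 − R²)).

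- R² = 0: 2.45, power 64.5%.
- R² = 0.1: 2.58, power 69.0%.
- R² = 0.2: 2.74, power 74.1%.

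**Step 5: simulation with imperfect balance.** Two separate runs under the assumptions above gave this power at 1.0 SD, t test versus two-factor model:

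| R² | Run 1 | Run 2 |
|---|---|---|
| 0 | 64.5% vs 63.9% | 64.7% vs 64.1% |
| 0.1 | 65.6% vs 68.9% | 67.3% vs 70.3% |
| 0.2 | 65.8% vs 73.5% | 66.9% vs 73.8% |

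The differences are −0.6 point in both runs at R² = 0, then 3.3 and 3.0 points at 0.1, and 7.7 and 6.9 points at 0.2.

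The t test's type I error in run 1 was 4.9%, 4.1% and 3.0% at R² = 0, 0.1 and 0.2; run 2 gave 3.3% at 0.2. The adjusted model stayed between 4.7% and 5.2% in run 1. A run with a weaker biased coin (0.8) and prevalences of 0.35 and 0.40 gave t-test errors of 5.2%, 3.7% and 3.1%, so the result does not hinge on those two assumptions.

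**Step 6: the planned regression as it stands.** It also contains sex, which allocation does not balance. With a non-predictive sex term added to group, age and eGFR, power at R² = 0 was 61.2% against 64.7% for the t test, a cost of 3.5 points. In a further run at R² = 0.1 it was 66.3% against 66.0%, no real gain. The gains in step 5 therefore belong to the model without sex.

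**The case against.** **The error is on the safe side.** This stands. The estimate is unbiased and type I error stays at or below about 5%. The t test's own power does not fall as R² rises (64.5% to 65.8% in run 1). What is forgone is a possible gain. A reader might infer that the result would be biased or false positives inflated; neither follows.

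**A useful R² is not shown.** This also stands. The surrogate-marker remark concerns the level of indoxyl sulfate, whereas the endpoint is within-patient change. Differencing removes whatever part of the eGFR association is stable over 8 weeks. Nothing in the article shows that the two factors explain 10% or 20% of the variance of change, for this or any secondary endpoint.

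**Adjustment is already planned for the primary endpoint.** Partly. The regression covers both factors, but it is not the primary test, and a treatment term is not stated. That silence does not show the term is absent. Adjusted models for secondary endpoints may sit in an analysis plan not shown, so the point rests on the test the article does name for them.

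**The future trial.** A reader might infer that the variance carried into the next trial's design would be too large. It would not. In simulation the mean pooled within-arm variance was 1.002 and 1.006 at R² = 0.1 and 0.2, against a true value of 1. That is the correct marginal variance for planning an unadjusted comparison. Only the standard error of this trial's difference is overstated.

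**Conclusion.** The mismatch between allocation and main analysis is real, and its effect is modest and conditional. If age group and eGFR group explain 10% to 20% of the variance of the 8-week change, the nominal 5% t test runs at about 4% to 3%, and about 3 to 7 points of power are forgone at an assumed 1.0 SD effect with 12 per arm. If they explain nothing, nothing is lost. The R², factor prevalences, biased-coin probability and effect size are all assumptions; only the design and the tests come from the article. In a pilot sized on feasibility, this is a cheap efficiency improvement, not a threat to validity.

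**What to change.** State the primary analysis as a linear model of the baseline-to-week-8 change in serum indoxyl sulfate on treatment group plus the two minimization factors, age and eGFR, without sex. The figures above assume the factors enter in the categories used for allocation. Use the same form for the continuous secondary endpoints. Keep the unpaired t test and the regression that includes sex as sensitivity analyses, and state that the latter contains treatment group.

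**Cost:** two degrees of freedom (22 to 20), under 1 point of power if the factors do not matter, and no new data, since both are collected for allocation. It is more than an edit, however. The Discussion reports an approved, registered trial with 19 patients enrolled by the end of August 2023, and the trial is open-label. The change should go through as a documented, dated amendment before outcome data are examined.

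### No stated analysis of serum indoxyl sulfate adjusts for its own baseline value; ANCOVA would usually be more precise, at almost no cost

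*Protocol article*

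**What the plan says.** The Endpoints section defines the outcome as a change: "the primary endpoint is the change in serum indoxyl sulfate concentration at baseline and at 8 weeks". The Statistical analysis section then names three analyses.

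- **Primary:** unpaired t "tests for the measurement changes from baseline to week 8 between the intervention and control groups". The same test is applied to the secondary endpoints.
- **Repeated measures:** "the changes between the intervention and control groups at baseline, 8 and 12 weeks will be tested using repeated measures analysis of variance". Baseline enters here as one of the outcome time points, not as a covariate.
- **Supportive regression:** a model for the week-8 change in indoxyl sulfate "using age, sex, and eGFR at baseline as covariates".

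Baseline serum indoxyl sulfate is not a covariate in any of them. Table 2 and the Data and sample collection section show that it is measured at baseline, week 8 and week 12. Minimization uses two factors: "The allocation ratio is set at 1:1, with allocation adjustments for age" and, in the same sentence, eGFR. It does not use indoxyl sulfate.

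**The concern.** Analysing a raw change score fixes the slope of week 8 on baseline at 1. With equal variances at both visits, the slope that removes the baseline contribution is rho, which is below 1. The change score then over-corrects: an arm that starts higher by chance will tend to show the larger fall, through regression to the mean.

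The repeated-measures ANOVA does not avoid this, because its baseline-to-week-8 contrast between groups is again a change-score contrast. The supportive regression models the same change and omits this covariate.

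What is at stake is the precision of the main estimate from a 24-patient pilot that, according to the Discussion and Conclusion, will inform the design of a later randomized trial. The method and the covariate list are both stated, so this is a choice the plan has made and not a detail left to a fuller document.

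**Working it through.** **Inputs from the article.** Sample size: "The sample sizes for the intervention and control groups will be 12 cases each". Two-sided test at p < 0.05. Age and eGFR are the minimization factors. No effect size, SD or power is stated; the size rests on feasibility and pilot-study guidance. The only design figure to reproduce is 12 + 12 = 24, which agrees.

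**Assumptions, not in the article.** Rho from 0.5 to 0.95, the same SD s at both visits, and normal data.

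**Step 1: variance of the estimated group difference, n per arm.**

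- Change score: 2(1-rho)s² × (2/n).
- ANCOVA: (1-rho²)s² × (2/n) × [1 + 1/(2n-4)]. At n = 12 the bracket is 1 + 1/20 = 1.05, the average cost of estimating the slope.
- Ratio, change score over ANCOVA: [2/(1+rho)] / 1.05.

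| rho | 2/(1+rho) | net ratio | participants equivalent to the gain, 24 × (net ratio - 1) |
|---|---|---|---|
| 0.5 | 1.33 | 1.27 | 6.5 |
| 0.6 | 1.25 | 1.19 | 4.6 |
| 0.7 | 1.18 | 1.12 | 2.9 |
| 0.8 | 1.11 | 1.06 | 1.4 |
| 0.9 | 1.05 | 1.00 | about 0 |
| 0.95 | 1.03 | 0.98 | slight loss |

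Break-even is where (1+rho)/2 × 1.05 = 1, so rho = 2/1.05 - 1 = 0.905.

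**Step 2: power and interval width.** The reference effect is the one that the change-score t test detects with 80% power at 12 per arm (noncentral t): 1.20 SDs of change. In 40,000 simulated trials per value of rho, ANCOVA had power 88%, 86%, 84%, 82%, 80% and 79% at rho 0.5, 0.6, 0.7, 0.8, 0.9 and 0.95. The ratio of mean confidence-interval widths, ANCOVA to change score, was 0.89, 0.92, 0.95, 0.97, 1.00 and 1.01.

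**Step 3: chance imbalance.** Under simple randomization the baseline mean difference D has SD s√(2/12) = 0.41s, and exceeds 0.5s in either direction in about 22% of trials. Given D (intervention minus control), the change-score estimate is shifted by -(1-rho)D. The SD of that shift is 0.5 × 0.41s = 0.20s at rho 0.5 and 0.3 × 0.41s = 0.12s at rho 0.7.

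This is not a second harm on top of Step 1. In units of s²(2/n), 2(1-rho) = (1-rho²) + (1-rho)². At rho 0.7 that is 0.60 = 0.51 + 0.09. The 0.09 is the imbalance component: 0.09 × 2/12 = 0.015, whose square root is 0.12. It is already inside the change score's standard error.

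**Step 4: how far eGFR stands in for the missing covariate.** Suppose week-8 indoxyl sulfate depends on eGFR only through baseline indoxyl sulfate, and the two baselines correlate at -0.4 to -0.7 (assumed). At rho 0.7, adjusting for eGFR then lowers the variance of change by 2% to 7%. Adjusting for baseline indoxyl sulfate lowers it by 15%. Both are large-sample figures.

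**The case against.** The strongest reply is that nothing here is invalid. The endpoint is defined as a change, and a t test on change matches it. Under randomization the test is unbiased, with the intended type I error. That stands. A reader might infer that the planned test is biased, but the shift in Step 3 is a mean-zero chance component. It matters only conditionally, for the trial actually obtained.

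A reader might also infer that baseline imbalance will be large relative to the effects sought, or that ANCOVA wins at any correlation. The article supports neither. It gives no effect size or SD against which to judge the imbalance. At 24 patients the gain ends near rho 0.90.

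Other points stand in part:

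- **Rho may be high.** The run-in restrictions and the defined meals before blood sampling could reduce within-person variation. At rho 0.7 to 0.8 the interval narrows by only about 3% to 5%.
- **Equal variances are assumed.** If the week-8 SD is 1.2 times the baseline SD and rho is 0.8, the slope is 0.96. The change variance is 1 + 1.44 - 1.92 = 0.520 and the ANCOVA residual variance is 1.44 × 0.36 = 0.518. There is then no gain to set against the 5% cost.
- **There is partial protection already.** Minimization on eGFR, and eGFR in the regression, help if eGFR and indoxyl sulfate are correlated. The figure of 0.41 is then an upper one.
- **The change is not trivial procedurally.** The protocol is approved and registered, the trial is open-label, and 19 patients had been enrolled by the end of August 2023.
- **It is a pilot with no power claim,** so no stated figure is wrong.

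These points limit the size of the gain. They do not give a reason to leave out a baseline that is already scheduled for everyone: in the table the largest loss is about 2% in variance, while the gain at moderate rho is several times that.

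**Conclusion.** The point holds as a recommendation for efficiency, not as an error in the plan. On the equal-variance assumption, the planned primary test has a variance 6% to 27% larger than ANCOVA for rho from 0.8 down to 0.5, is level with it at about 0.90, and is marginally better above that. The conditional shift of -(1-rho)D is the same loss seen in a single trial. The SD of D is at most about 0.41 baseline SDs, and lower to the extent that minimization on eGFR also balances indoxyl sulfate. All of these sizes depend on rho, which the article does not give. The change is worth making but not essential to the trial's validity.

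**What to change.** By amendment before database lock:

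1. Make the primary analysis an ANCOVA of week-8 serum indoxyl sulfate (or its change from baseline; with baseline in the model the group difference is the same) on allocated group, with baseline serum indoxyl sulfate as covariate. Report the adjusted difference with its 95% CI.
2. Use the same form, each outcome's own baseline as covariate, for the continuous secondary endpoints.
3. Add baseline indoxyl sulfate to the supportive regression and keep the covariate list short. Group, baseline, age, sex and eGFR plus an intercept is six parameters on 24 patients, and baseline indoxyl sulfate may overlap with eGFR.
4. Keep the unpaired t test on change as a sensitivity analysis.

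Because the trial is open-label and recruiting, the amendment should record its date and that it was made without sight of outcome results by arm. The cost is one degree of freedom in the primary analysis and a small amendment. No new data or visits are needed.

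### The primary t test on absolute change leaves baseline indoxyl sulfate unused; a baseline-adjusted analysis on a prespecified scale would generally be more efficient and easier to interpret

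*Protocol article*

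**What the plan says.** The Endpoints section states that "the primary endpoint is the change in serum indoxyl sulfate concentration at baseline and at 8 weeks". The Statistical analysis section tests it, and the secondary endpoints, with unpaired t "tests for the measurement changes from baseline to week 8 between the intervention and control groups", two-sided at 0.05. No log, ratio or percentage scale is named, so the plain reading is absolute change.

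The same section adds a regression of that change on age, sex and baseline eGFR. Baseline indoxyl sulfate is not among the covariates.

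Three other places bear on this:
- Eligibility criteria admit "estimated glomerular filtration rate (eGFR): 15 to <60", a range of 60/15 = 4-fold.
- Endpoints calls indoxyl sulfate "a metabolite of intestinal origin, and a surrogate marker of renal function".
- Sample size says "The sample sizes for the intervention and control groups will be 12 cases each" and "The number of cases is set based on feasibility and the recommended number of cases for the pilot study". No effect size, SD or power is given.

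Randomization is by minimization on age and on eGFR (15 to <30, 30 to <60).

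**The concern.** A marker of renal function measured across a fourfold eGFR range is likely to show wide differences between patients at baseline. A change score then makes an untested choice: it subtracts the whole baseline value, as if the slope of week 8 on baseline were exactly 1. Estimating that slope uses data already collected and is usually more precise. With 12 per arm there is little precision to spare: by the noncentral t, 80% power needs a standardised difference of about 1.2.

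The scale is a second, separate question. The Introduction places the mechanism in the gut, with toxins passing from there into blood. If the level is roughly production divided by clearance (an assumption), a cut in production lowers the concentration more, in absolute units, where clearance is low. A mean absolute change then depends on the eGFR mix of the sample and transfers less well to the later trial that this pilot is meant to inform.

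**Working it through.** **The plan's own figure.** 12 per arm cannot be reproduced from a formula, because no effect size, SD or power is stated.

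**Why baseline adjustment helps.** With equal variance σ² at both visits and correlation ρ, the change score has variance 2σ²(1−ρ) and ANCOVA has residual variance σ²(1−ρ²). The ratio of ANCOVA to change score is (1+ρ)/2. For assumed ρ of 0.6, 0.8 and 0.9 this is 0.80, 0.90 and 0.95. The price is one degree of freedom: 24−2 = 22 becomes 24−3 = 21.

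**Simulation.** From the document: 12 per arm, two-sided 0.05. All else is assumed:
- True levels are log-normal with median 1 and between-patient CV 0.5, 0.7 or 0.9.
- Within-patient SD is 0.25 or 0.35. Error is proportional (on the log scale), additive (in units of the median level), or mixed (0.7 of the SD from each source).
- The effect is either a 30% reduction or a constant fall of 0.3 median units.
- Values are floored at 0.05, which affects the log analyses under additive error.
- 20,000 trials per cell.

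Power in %, as the range over the six CV and SD combinations. The last column is the range of within-cell gains, in percentage points.

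| Effect | Error | t on change | ANCOVA, raw | ANCOVA, log | Raw ANCOVA minus t |
|---|---|---|---|---|---|
| 30% | proportional | 21–47 | 27–59 | 41–68 | 6.2 to 12.0 |
| 30% | mixed | 28–52 | 33–62 | 25–54 | 5.4 to 10.5 |
| 30% | additive | 34–60 | 41–68 | 21–45 | 5.5 to 8.2 |
| constant | proportional | 16–43 | 19–48 | 47–74 | 3.1 to 5.8 |
| constant | mixed | 19–46 | 21–50 | 28–52 | 2.4 to 4.7 |
| constant | additive | 26–50 | 27–52 | 21–43 | −0.5 to 3.5 |

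With no effect, the rejection rate was 3.8–5.3% for all three analyses.

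**Reading the table.** Raw-scale ANCOVA matches or beats the t test in every row, to within simulation error. The log scale does not: it wins clearly under proportional error and loses under additive error. Under mixed error it is within a few points of the t test for a 30% effect (for example 46% against 49% at CV 0.7, SD 0.25) and ahead of it for a constant effect (49% against 39% in the same cell).

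**Do a few patients dominate?** A second simulation drew eGFR uniformly over 15–60 with level proportional to 1/eGFR. Under proportional error and effect, the 6 of 24 patients with the highest baseline carried 49–69% of the within-arm sum of squares of absolute change; an even share is 6/24 = 25%. Under additive error and effect they carried 26–31%. With eGFR held constant and proportional error (log SD 0.3), absolute change still trailed the log ratio: 42% against 50% power with no other spread, and 35% against 51% with between-patient log SD 0.5. So the eGFR range explains only part of any loss.

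**The case against.** The strongest case against has four parts.

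- The transformation of a biomarker is often fixed in an analysis plan, and none is shown here. That is fair for the scale. It does not cover the primary test, which the article names, or the covariate list, which it also names and which omits baseline indoxyl sulfate.
- A difference in mean concentration is a legitimate effect measure, and the t test is valid. Both stand. The simulated size stays near 5%.
- Minimization on eGFR works against one arm collecting the high-level patients, and the planned regression adjusts for eGFR. This largely answers any worry about chance imbalance. It does not replace adjustment for the baseline of the outcome itself, nor remove unequal variance between patients.
- This is a pilot whose size rests on feasibility, so no promised power is missed. That limits the consequence. Still, the plan runs a formal test at 0.05, and its results are to shape a later trial.

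A reader might infer more: that a few high-level patients do dominate the primary test, that power is lost for want of a log scale, or that the result hinges on which arm holds those patients. The documents do not support this. They give no indoxyl sulfate values, SD or distribution. Dominance and loss follow only if within-patient variation scales with level, and the ranking of the scales reverses if it does not. Skewed levels alone do not settle it; the error structure does.

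**Conclusion.** The point holds as one of efficiency and interpretability, not validity. The firmer part is baseline adjustment: about 5 to 12 points of power for an assumed 30% reduction, whichever error model applies. The gain falls to roughly 0 to 6 points if the effect is a constant absolute amount.

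The scale is conditional. Under proportional error, log ANCOVA roughly ranges over 41–68% where the t test has 21–47%. Under mixed error the advantage largely disappears or depends on the type of effect. Under additive error it reverses. All SDs, effect sizes and error models are assumptions, so these figures show a range and do not predict this trial's power.

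**What to change.** Before results are seen:

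1. Make the primary analysis an ANCOVA of week 8 indoxyl sulfate on group with baseline indoxyl sulfate as covariate, reported with a 95% CI. Add baseline indoxyl sulfate to the existing multivariable model as well. The change-score t test can stay as a supporting analysis.
2. Prespecify the scale and give the reason, for example assay or repeat-measurement data on how variation relates to level. If variation is expected to be proportional, model log(week 8) on group and log(baseline), report the ratio of geometric means with 95% CI, and show the raw-scale analysis as sensitivity. Do not choose the scale by a normality test on the trial data.
3. Limit any log scale to concentration endpoints. It should not be applied to pH, the questionnaires or the microbiome.

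The cost is wording and one degree of freedom; no new data or patients are needed. On the log scale the effect becomes a percentage rather than a concentration difference, which is the main drawback.
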